# Tongmai Yangxin intervening in myocardial remodeling after PCI for coronary heart disease: study protocol for a double-blind, randomized controlled trial

**DOI:** 10.1186/s13063-020-4208-4

**Published:** 2020-03-20

**Keywords:** Traditional Chinese medicine, Tongmai Yangxin pill, Myocardial remodeling, Acute myocardial infarction

## Abstract

**Background:**

Coronary heart disease (CHD) has become a common cardiovascular disease that seriously threatens the health of people. As reperfusion in the early phase and drug therapy, especially percutaneous coronary intervention (PCI), have become widely used in the clinic, the mortality of acute myocardial infarction in the short term has been reduced significantly. In addition, in 40%–56% of patients who experience myocardial infarction, cardiac dysfunction occurs and about 25%–33% develop heart failure.

**Methods:**

This study was designed as a multicenter, double-blind, randomized, placebo-controlled, parallel-group, superiority trial. Participants were randomly assigned in a 1:1 ratio through a centrally controlled, computer-generated, simple randomization schedule. The primary outcome was left ventricular end-diastolic volume index = left ventricular end-diastolic volume/body surface area. The combined secondary outcomes include traditional Chinese medicine syndrome score, echocardiogram results, 6-minute walk test results, Seattle Angina Questionnaire score, cardiac magnetic resonance imaging results, biological indicators, dynamic electrocardiogram results, and experiment event rate. Assessments will be performed at baseline and at 4, 8, and 12 weeks after randomization.

**Discussion:**

This trial will demonstrate that the addition of a Tongmai Yangxin pill (TMYX) to conventional treatment will intervene in the development of cardiac remodeling and cardiac dysfunction.

**Trial registration:**

This study was registered in the Chinese Clinical Trial Registry on 7 May 2019. The registration number is ChiCRT1900023023 (http://www.chictr.org.cn/showproj.aspx?proj=12370).

## Introduction

Coronary heart disease (CHD) has become a common cardiovascular disease that seriously threatens the health of people. The data from the “Summary of the 2018 Report on Cardiovascular Diseases in China” showed that the number of individuals with cardiovascular diseases has reached 290 million, 11 million of whom have CHD, and 2.5 million have had a myocardial infarction (MI) [1]. As reperfusion in the early phase and drug therapy, especially percutaneous coronary intervention (PCI), have been widely used in the clinic, the mortality of acute MI (AMI) in the short term is reduced significantly. However, unluckily, an epidemiological investigation showed that, although the mortality of CHD has declined, the incidence of heart failure (HF) has increased year by year [2]. Over the past three decades, preventive and therapeutic agents have substantially improved the prognosis of AMI by normatively using β-blockers, angiotensin-converting enzyme inhibitors/angiotensin II receptor antagonists (ACEIs/ARBs), aldosterone receptor antagonists, and so on. However, a report showed that 40%–56% of the patients who experience MI will experience cardiac dysfunction and that about 25%–33% will develop HF [3, 4]. Cardiac remodeling is the key pathophysiological mechanism of angina pectoris, arrhythmia, and HF following MI.

Traditional Chinese medicine (TCM) has been used for thousands of years to treat CHD, as it is characterized by multiple components, and it can intervene and treat diseases through multiple pathways and targets. A number of clinical trials have demonstrated the unique advantage of TCM in the improvement of the clinical symptoms and evolution and prognosis of diseases [5]. However, effective herbal medicine with a high level of evidence is lacking for interventions in ventricular remodeling.

TMYX, formerly known as pill 651, which is composed of the classic formulas “Zhigancao Decoction” and “Sheng mai yin”, has been on the market since 1965 and is registered in the 2015 Chinese Pharmacopoeia. TMYX has been used for decades to cure CHD, chest pain, palpitation, angina, and irregular heartbeats. TMYX consists of 11 Chinese medicinal herbs: Radix Rehmanniae, Caulis Spatholobi, Radix Glycyrrhizae, Ramulus Cinnamomi, Radix Ophiopogonis, Radix Polygoni multiflori preparata, Asini Corii colla, Fructus Schisandrae, Radix Codonopsis, Capapax et Plastrum Testudinis, and Fructus Jujubae. A recent study identified 80 compounds from a TMYX, including flavonoids, coumarins, iridoid glycosides, saponins, and lignans, exhibiting anti-inflammatory activity [6]. A clinical study by Xuemeng Cai et al. [7] indicated that TMYX in the treatment of stable coronary artery disease may be involved in energy metabolism, amino acid metabolism, oxidative stress, and inflammation.

Therefore, TMYX is worth investigating in patients who have experienced AMI and who received PCI because of pleiotropic effects. The assumption is made that TMYX in addition to standardized Western medications may be superior to intervene in myocardial remodeling, decrease the rate of cardiac dysfunction, and delay the occurrence of HF.

## Methods/design

### Study objectives

The study objective is to prove the hypothesis that TMYXP in addition to standardized Western treatment is more effective than standardized Western treatment alone in reducing left ventricular end-diastolic volume index (LVEDVI), intervening in myocardial remodeling after PCI for AMI.

### Design overview

This study was designed as a multicenter, double-blind, randomized, placebo-controlled, parallel-group, superiority trial. Eight clinical centers from different regions of China will participate in this trial, including the First Affiliated Hospital of Henan University of Chinese Medicine, the First Affiliated Hospital of Guangzhou University of TCM, Guangdong Provincial Hospital of Traditional Chinese Medicine, the Second Affiliated Hospital of Tianjin University of Traditional Chinese Medicine, Guang’anmen Hospital of the China Academy of Traditional Chinese Medicine, Shuguang Hospital Affiliated to Shanghai University of Traditional Chinese Medicine, and the First Affiliated Hospital of Xinxiang Hospital. All of the researchers of the participating organizations are responsible for data collection and quality. Data management and statistical analyses will be performed solely by data handlers and data analysts at the Institute of Basic Research in Clinical Medicine, China Academy of Chinese Medical Sciences. This study will abide by the Declaration of Helsinki and has been subjected to vetting by the ethics committee of the First Affiliated Hospital of Henan University of TCM (ethics approval number: 2019HL-048-01). As of October 10, 2019, this study was approved by the ethics committees of seven centers (ethics approval numbers: 2019HL-048-01, 2019–095-KY-04, K[2019]041, 2019–693–48-01, 2019–091-01, 2019164, and BF2019–085-01). We will not begin recruiting at other centers in the trial until local ethical approval has been obtained. This study has also been registered with the Chinese Clinical Trial Registry (ChiCRT1900023023). All study subjects must sign and date informed consent documents prior to randomization. A flow diagram of the study procedures is illustrated in Fig. 1.

**Fig. 1 Fig1:**
[figure not shown]
Study design of the Tongmai Yangxin pill (TMYX) trial

### Recruitment

We will set up recruitment advertisements to ensure that the subjects are recruited on time. Participants will be recruited through Internet advertisements and posters in the community and at selected hospitals until the whole trial is complete. [name], who participated in the revision of the manuscript, will manage the responses to the advertisements and posters, and the researchers who have a Good Clinical Practice certificate will recruit patients.

### Inclusion criteria

This trial will recruit participants who satisfy the following conditions:
Patients with acute anterior MI who, within 10 days, underwent emergency PCI, underwent PCI after emergency thrombolytic therapy, or received elective PCI.Patients who meet the syndrome differentiation standard of TCM with combined deficient Qi and Yin blood stasis.Patients who are 18 to 75 years old, both male and female.Patients who voluntarily sign informed consent forms.

### Exclusion criteria

This trial will exclude patients who meet any one of the following criteria:
Patients with multiple coronary artery branch lesions who did not receive elective PCI within 10 days.Patients with AMI with severe complications, such as acute HF, cardiogenic shock (conventional treatment cannot correct), or mechanical complications.Patients with AMI with HF, Killip classification III or IV (Killip classification for AMI:
Class I: no symptoms or signs;Class II: has symptoms and signs, rales of not more than 50%, S3 gallop, x-ray pulmonary congestion;Class III: severe pulmonary edema, rales of at least 50%;Class IV: cardiac shock.)Patients with chronic HF or previous anterior MI in their medical history.Patients with other diseases, such as cardiomyopathy, rheumatic heart disease, valvular heart disease (severe stenosis/incomplete closure), arrhythmia (persistent atrial fibrillation/atrial flutter, third-degree A-V block, sick sinus syndrome, or arrhythmia after the implantation of a pacemaker), hyperthyroidism, cardiac tamponade, pulmonary arterial hypertension, acute paroxysmal asthma/chronic obstructive pulmonary disease, or severe infection.Patients with severe liver and kidney function impairment (alanine aminotransferase (ALT), aspartate transaminase (AST), or total bilirubin more than three times the upper limit of normal reference value, creatinine (Cr) of at least 3 mg/dL or estimated glomerular filtration rate of not more than 60 mL/min·1.73 m^2^), patients with severe primary diseases of the hematopoietic system, or patients with mental diseases.Patients with malignant tumors.Patients with an allergic constitution or allergy to multiple drugs or foods or patients with an allergy to known components of the study drugs.Patients who cannot take care of themselves or cannot receive oral drugs.Patients who have participated in other drug clinical trials within 1 month.Patients with a suspected or known history of alcohol or drug abuse.Pregnant or lactating women or those who plan to be pregnant.Subjects who, in the judgment of the researcher, are not suitable for study observation.

### Randomization process

The randomized program was provided by statistical professionals from the Institute of Basic Research in Clinical Medicine, China Academy of Chinese Medical Sciences. Participants were randomly assigned in a 1:1 ratio through a centrally controlled, computer-generated, simple randomization schedule. To ensure the smooth progression of the study, the method of competing to recruit participants will occur at eight centers. This study design includes placebo-controlled and double-blind methods. All of the experimental drugs will be packed, obeying the principles of a random assignment table, and will be blinded. The blinding code will be duplicated and will be individually sealed and stored at the sponsor organization and drug clinical trial institution. The study drugs are labeled with serial numbers; when the subject’s random number is generated, the corresponding number of drugs will be transported to the destination within 24 h. All participants, care providers, attending physicians, laboratory staff, and biostatisticians will be blinded to treatment assignment until the database has been locked. Randomization was completed in July 2019. The last participant is expected to be enrolled in December 2020.

### Blinding

This study will blind researchers, participants, evaluators, doctors, nurses, and statistical experts. The blinding codes have been placed in a sealed envelope and will be revealed only when adverse events (AEs) occur or at the terminal analysis.

### Interventions

Eligible participants will be allocated to receive TMYX or placebo (for 12 weeks) in addition to standardized Western treatment. The dose of the drugs, including antiplatelets, stains, ACEIs/ARBs, β-blockers, anti-ischemics, must be in keeping with “the guidelines of acute myocardial infarction in participants presenting with ST-segment elevation”, which was formulated by the Chinese Society of Cardiology in 2015. The TMYXP and placebo were produced and packed in a single batch (production batch number: Tongmai Yangxin: 1070649; Placebo: 20190214) by Tianjin Zhongxin Pharmaceutical Group Co., Ltd., Le Ren Tang Pharmaceutical Factory, which has no conflicts of interest relevant to this study. The test results of drug quality were consistent with the Chinese Medicine Standards of the State Food and Drug Administration. The placebo is composed of 5% crude TMYX and 95% starch, which have the same appearance and scent as the active treatment drugs. Participants will take one bag at a time orally twice daily for 12 weeks, and other Chinese medicine will be avoided in the meantime.

### Outcomes

The primary outcome is LVEDVI = left ventricular end-diastolic volume/body surface area (LVEDV/BSA) and will be detected by three-dimensional ultrasound. The combined secondary outcomes include TCM syndrome score, echocardiogram results, 6-minute walk test results, Seattle Angina Questionnaire score, cardiac magnetic resonance imaging (CMRI) results, biological indicators (growth stimulation expressed gene 2 [ST2], galactose-specific lectin 3 [galectin-3], NT-proBNP, IL-1β, CRP, TNF-α, MMP-2, MMP-9, TIMP-1, TGF-β1, and CTGF), dynamic electrocardiogram results, and experiment event rate (hospitalization rates for HF, death rate of cardiovascular disease, or MI).

### Safety assessment

Safety assessment will be based on the incidence of AEs, including clinically significant changes in physical examinations, vital signs (including blood pressure, heart rate, and pulse), and laboratory examinations. Laboratory examinations to be performed include routine blood and urine parameters, liver and kidney profiles, electrolytes, and myocardial enzymes (detailed monitoring schedule in Table 1). Women of childbearing age will be tested for pregnancy by urine examination at enrollment. The National Cancer Institute’s Common Terminology Criteria for Adverse Events (CTCAE) version 5.0 grading system will be used to classify the nature and severity of AEs [8].

**Table 1 Tab1:** Research flowchart

Item	Research phase			
	Screening/enrollment	Follow-up		
Time	Before enrollment	4 weeks after enrollment	8 weeks after enrollment	12 weeks after enrollment
	V0	V1	V2	V3
Confirm inclusion and exclusion criteria	√			
Signed informed consent	√			
Basic information	√			
Medical history, treatment history, and allergies	√			
Current medications	√			
Retrieve central randomization	√			
**Efficacy evaluation**				
Echocardiogram	√	√		√
Cardiac magnetic resonance imaging		√		√
Biological indicator	√	√	√	√
Dynamic electrocardiogram	√	√	√	√
Traditional Chinese medicine syndrome score	√	√	√	√
6-minute walk test	√	√	√	√
Seattle Angina Questionnaire	√	√	√	√
Experiment event rate		√	√	√
**Safety**				
Blood pressure, heart rate, etc.	√	√	√	√
Routine blood and urine parameters	√	√	√	√
Liver and kidney profile	√	√	√	√
Electrolytes	√	√	√	√
Myocardial enzymes	√	√	√	√
Urine pregnancy test	√			
Electrocardiogram	√	√	√	√
Appointment for next follow-up		√	√	
Study completion status				√
Case report form examination				√

### Follow-up protocol

The follow-up for all participants will be scheduled at 4, 8, and 12 weeks. The primary and secondary outcomes as well as safety will be evaluated at each follow-up. AEs, especially severe AEs, are to be reported to the research group committee and ethics committee within 24 h. If the principal investigator determines that the AEs may be related to the experimental drugs, the blinding code will be opened and the testing of this subject will be terminated at the same time. All of this must be recorded on the case report form (CRF) and noted to the monitors.

### Compliance

Economic compensation (including transportation, food, and communication reimbursement) is necessary for participants at each follow-up appointment. In addition, at least two telephone numbers will be required to be provided by every participant so that they can be contacted at any time. Moreover, attending physicians will be responsible for answering each patient’s questions. In addition, all of the participants will be compensated 100 Chinese yuan.

To assess adherence to medication, the participants will be asked to fill in the T cards truthfully and to return the unused pills and packages. Non-adherence is defined as when more than 20% of the total amount of medication is not taken as required. The reasons for non-adherence will be recorded in detail on the CRF.

### Sample size estimation

Sample size was calculated on the basis of the expected reduction in LVEDVI after treatment for 3 months. A previous study suggested that the LVEDVs of AMI patients within 24–72 h are approximately 162 ± 57 mL and 162 ± 57 mL at 6 months [9]. According to the pilot experiment of TMYX, the LVEDVI may be reduced by 4 mL/m^2^ within 3 months. Given that the LVEDVI will fall 4 mL/m^2^ following treatment with TMYX added and given a type I error rate of α of 0.05 and power (1 − β) of 0.90, all of the subjects will be assigned in a 1:1 ratio to the treatment group or control group. There should be 100 participants for each arm. Given a dropout rate of less than 20%, a total of 240 participants will be needed to be allocated for the efficacy analysis.

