### Statistical approach

Statistical analysis will be performed by using SPSS 21.0 by third-party companies that have no access to the blinding codes, and we will not perform any subgroup analyses. If the primary outcome measure has superior efficacy in one group over the other, a confidence interval will be used for analysis. The secondary end point will be analyzed by a two-tailed test, and significance level will be α of 0.05 (otherwise stated). Continuous variables will be described by the mean and standard deviation. Categorical data will be described by the percentage, frequency, and composition ratio. All effectiveness and safety analyses will be strictly conducted in accordance with the intention-to-treat principle, the full analysis set (FAS) population, the per protocol set (PPS) population, and the safety set (SS) population. A *P* value of less than 0.05 will be considered statistically significant [10].

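### The stated 90% power with 100 per arm for a 4 mL/m² difference in LVEDVI does not follow from the planning figures the protocol prints

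*Protocol article*

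**What the plan says.** All the planning figures are in the protocol article, Sample size estimation.

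- **Variability:** the section cites an earlier study in which "the LVEDVs of AMI patients within 24–72 h are approximately 162 ± 57 mL and 162 ± 57 mL at 6 months". This is the only SD in the document. It refers to LVEDV in mL, at single time points.
- **Effect:** the 4 mL/m² comes from a pilot ("According to the pilot experiment of TMYX") and enters the calculation as "Given that the LVEDVI will fall 4 mL/m^2^ following treatment with TMYX added".
- **Error rates:** "given a type I error rate of α of 0.05 and power (1 − β) of 0.90".
- **Result:** "There should be 100 participants for each arm", raised to 240 in total for dropout.

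The Outcomes section defines the endpoint on a different scale from the quoted SD: "The primary outcome is LVEDVI = left ventricular end-diastolic volume/body surface area (LVEDV/BSA"). Sidedness is stated only in Statistical approach, and only for other endpoints: "The secondary end point will be analyzed by a two-tailed test". The Study objectives section sets the aim as superiority of the add-on treatment over standardized Western treatment alone, which is a comparison between arms.

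**The concern.** A two-sample calculation for means needs a difference, an SD, alpha and power. The section prints three of these and a sample size, so the SD it must have used can be recovered and compared with the SD it quotes. The two are far apart.

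The effect has a second problem. A fall in LVEDVI on active treatment equals the difference from control only if control LVEDVI does not change over 12 weeks. The only figures that bear on this are the two LVEDV values, and the later one is at 6 months.

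At stake is how the result will be read. A null result from a trial described as having 90% power counts as fairly strong evidence against a 4 mL/m² effect. If the planning SD is not the one that applies, that reading is unsafe.

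**Working it through.** **Inputs from the protocol:** difference d = 4 mL/m²; alpha 0.05; power 0.90; n = 100 per arm, 1:1; SD of LVEDV = 57 mL.

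**Assumptions (not in the protocol):** body surface area (BSA) 1.6–2.0 m²; baseline-to-week-12 correlation r as shown; both one- and two-sided alpha, since sidedness is not stated for the primary outcome.

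**Step 1. SD implied by the stated sample size.** From n = 2(z_α + z_β)²SD²/d², SD = d√(n/2)/(z_α + z_β).

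- Two-sided: 4 × √50 / 3.2415 = 8.73 mL/m².
- One-sided: 4 × √50 / 2.9264 = 9.67 mL/m².

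**Step 2. SD from the quoted figure.** 57/1.6 = 35.6 and 57/2.0 = 28.5 mL/m². Against 8.73, the ratio is 3.3 to 4.1.

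**Step 3. Results at the quoted SD, unadjusted.** Power = Φ(d/(SD√(2/n)) − z_α).

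| | BSA 1.6 | BSA 2.0 |
|---|---|---|
| SD (mL/m²) | 35.6 | 28.5 |
| d/(SD√(2/100)) | 0.794 | 0.992 |
| Power, two-sided | 12.2% | 16.7% |
| Power, one-sided | 19.7% | 25.7% |
| Power, two-sided, 120 per arm with no dropout | 13.8% | 19.1% |
| n per arm for 90% power, two-sided | 1,667 | 1,067 |
| n per arm for 90% power, one-sided | 1,359 | 870 |
| Difference detectable with 90% power, two-sided, 100 per arm (mL/m²) | 16.3 | 13.1 |

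The noncentral t distribution gives 12.1% and 16.5% for the two-sided power at 100 per arm.

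**Step 4. Baseline adjustment.** The SD becomes SD√(1 − r²). Two-sided power:

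| r | BSA 1.6 | BSA 2.0 |
|---|---|---|
| 0.7 | 20% | 28% |
| 0.9 | 44% | 62% |

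Reaching 90% requires r = √(1 − (8.73/SD)²), which is 0.970 at BSA 1.6 and 0.952 at BSA 2.0.

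**Step 5. If indexing removes much of the spread.** Dividing each patient's volume by that patient's own BSA can remove variance due to body size. Take SD = 16 mL/m² purely as an illustration. Unadjusted two-sided power is Φ(4/(16 × 0.1414) − 1.96) = Φ(−0.19) = 42%. The correlation that restores 90% is √(1 − (8.73/16)²) = 0.84 two-sided, or √(1 − (9.67/16)²) = 0.80 one-sided.

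**Step 6. Definition of the difference.** Grant the implied SD of 8.73. If the active arm falls by 4 and control falls by 1 or 2 mL/m² (illustrative values), the between-arm difference is 3 or 2. Two-sided power is then 68% or about 36–37%.

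**The case against.** The strongest reply is that the protocol never says 57 mL was the SD used. The section bases the calculation on the expected reduction in LVEDVI at 3 months and takes the effect from a pilot. The relevant SD is then that of the change, or of the baseline-adjusted value, per m². It can be much smaller than the spread of unindexed volumes at one time point, and a value near 9 mL/m² would reproduce 100 per arm. The article also condenses a fuller protocol, where that SD may stand.

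This reply limits the point but does not remove it. A reader might infer that the trial's true power is 12–17%. The document does not support that: the figure depends on an SD that may not be the one used, on an assumed BSA and on an unadjusted two-sided test. Nor can one say that only a correlation of 0.95 or more would rescue the design, since Step 5 shows that about 0.84 suffices if the indexed SD is 16. What stands is that the article chose to print inputs and a result, and the printed inputs do not give the printed result. Condensation does not explain that.

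On the effect, one can read the 4 mL/m² as the extra fall over control, given the add-on design. The wording allows this but does not say it. A reader might also take the repeated 162 ± 57 for a copying error. An unchanged group mean and SD is possible, and the cited source is not at hand, so this is only something to check.

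**Conclusion.** The point holds as a failure of justification. With 100 per arm and alpha 0.05, the stated 90% power requires an SD roughly a third to a quarter of what the quoted figure gives at a BSA of 1.6–2.0 m². None of one-sided testing, the full 120 per arm, or baseline adjustment at correlations of 0.7–0.9 closes the gap on the quoted SD. Two things could close it: a correlation of about 0.95–0.97 (two-sided), or a materially smaller SD of LVEDVI or of its change. The article reports neither.

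Separately, the 4 mL/m² is a between-arm difference only if control LVEDVI is unchanged at 12 weeks, and the article offers only 6-month figures on that. Because the stated power governs how the primary result is interpreted and correction is cheap, it should be corrected.

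**What to change.** In the sample-size section:

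1. State the SD actually used (change in LVEDVI, or baseline-adjusted week-12 LVEDVI), its source, and whether alpha is one- or two-sided for the primary outcome.
2. Define 4 mL/m² as a between-arm difference, state the assumed control-arm change at 12 weeks, and check the repeated 162 ± 57 against its source.
3. Restate the power, or the difference detectable with 90% power, for the 240 patients planned.

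If no such SD exists, estimate it from the pooled enrollment (V0) and week-12 (V3) echocardiograms as they accrue, without unblinding, and restate power from that. Because arms are not compared, this spends no alpha.

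The cost is one rewritten paragraph and, if needed, one blinded SD calculation. Restating the power adds no patients. The downside is that the restated power may be less favourable than 90%.

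### The 240 to be allocated secures 100 per arm only up to 16.7% dropout, short of the ceiling of 20% that the plan allows for

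*Protocol article*

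**What the plan says.** All the figures are in the protocol article under Sample size estimation.

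- Design error rates: "given a type I error rate of α of 0.05 and power (1 − β) of 0.90".
- Allocation: "all of the subjects will be assigned in a 1:1 ratio to the treatment group or control group".
- Number required: "There should be 100 participants for each arm", so 200 in total.
- Allowance for loss and resulting total: "Given a dropout rate of less than 20%, a total of 240 participants will be needed to be allocated for the efficacy analysis".

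The dropout figure is an upper bound. The section gives no expected rate below it and does not show the formula that leads from 200 to 240.

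**The concern.** An allowance for dropout answers one question: how many must be allocated so that the required number remains after the losses planned for? Here the required number (200), the ceiling on loss (20%) and the total (240) are all printed, so the step can be checked directly. The total is what results from adding 20% of the required number. Losses are taken from the larger number allocated, so that sum falls short at the ceiling.

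What is at stake is the accuracy of the sample size statement. Readers and ethics committees will take it that 100 per arm, and with it 90% power, is protected for any dropout below 20%. For the upper part of that range it is not.

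**Working it through.** **Inputs, all from Sample size estimation**

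- Required: 100 per arm, 200 in total.
- Dropout: less than 20%; the ceiling d = 0.20 is used.
- Allocated: 240 in a 1:1 ratio, so 120 per arm on average. The randomisation is simple, so the actual split may differ slightly.
- α = 0.05 and power 0.90. The section does not say whether the sample size is one-sided or two-sided, so both are shown.

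**Step 1: reproduce the plan's figure.** Multiplying by (1 + d) gives 200 × 1.20 = 240, an exact match. That this formula was used is an inference from the match.

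**Step 2: the number that covers the ceiling.** Dividing by (1 − d) gives 200/0.80 = 250, or 125 per arm. The stated total is 10 lower.

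**Step 3: what 240 leaves.** The number remaining per arm is 120 × (1 − dropout).

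| Dropout | Total remaining | Per arm |
|---|---|---|
| 15% | 204.0 | 102.0 |
| 16.7% | 200.0 | 100.0 |
| 18% | 196.8 | 98.4 |
| 19% | 194.4 | 97.2 |
| 20% (ceiling) | 192.0 | 96.0 |

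The break-even rate is 1 − 200/240 = 16.7%.

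**Step 4: effect on power.** Take as given that 100 per arm yields 90% power. The expected value of the test statistic under the alternative is then z(1−α/2) + z(0.90) in the two-sided case. It is proportional to the square root of the number per arm, so going from 100 to 96 multiplies it by √0.96 = 0.9798. The effect size and the standard deviation cancel.

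- Two-sided: 1.960 + 1.282 = 3.242; 3.242 × 0.9798 = 3.176; power = Φ(3.176 − 1.960) = Φ(1.216) = 88.8%.
- One-sided: 1.645 + 1.282 = 2.926 (from unrounded values); 2.926 × 0.9798 = 2.867; power = Φ(2.867 − 1.645) = Φ(1.222) = 88.9%.

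Power at the ceiling is therefore about 89%, against the stated 90%.

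**The case against.** The best defence is that the plan sets a ceiling on dropout and does not predict a rate of 20%. Any rate up to 16.7% is also below 20%, and at those rates 240 does keep 100 per arm. This stands as far as it goes. A reader might infer that the printed figures can never be reconciled, or that the trial will fall short at its planned dropout. The text supports neither, because it names no planned rate and the figures fail only between 16.7% and 20%. The value of 96 per arm is the limit at the ceiling. The defence does not remove the point, however: an allowance stated as a ceiling should hold up to that ceiling, and nothing in the section suggests that 16.7% was meant.

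A reader might also infer that the plan presents 240 as the number analysed. The sentence says that "a total of 240 participants will be needed to be allocated for the efficacy analysis", which already marks 240 as the number allocated. It can fairly be read as allocating 240 in order to support the efficacy analysis, so there is no complaint about that wording.

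The power figure might be challenged because the section gives no standard deviation for the indexed volume. It quotes only 57 mL for the volume that is not indexed. A standard deviation can be back-solved from 100 per arm and a difference of 4 mL/m² (8.73 two-sided, 9.67 one-sided), but the document states neither value. The calculation above needs neither. It does rest on 100 per arm giving 90% power, which the printed inputs do not let a reader confirm.

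Finally, the effect is small. That is correct, and it limits the weight of the point without making the total right.

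**Conclusion.** The point holds in a limited form. The total of 240 matches inflation by multiplication and is 10 short of the 250 needed to keep 100 per arm at the 20% ceiling. It protects 100 per arm up to 16.7% dropout. Above that, and still within the stated allowance, the number remaining falls towards 96 per arm and power towards about 89%.

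The allocation and retention figures follow from the printed numbers alone, given an equal split and equal loss in the two arms. The power figure also assumes that 100 per arm gives 90% and uses the normal approximation. The validity of the trial is not threatened. What is wrong is a stated dropout tolerance that the allocation does not fully deliver.

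**What to change.** Keep 240 and correct the sentence in one of two ways:

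1. State that allocating 240 keeps 100 per arm for dropout of up to 16.7%.
2. Keep the 20% ceiling and state that at that rate about 96 per arm remain and power is about 89%, conditional on 100 per arm giving 90%.

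The first is the safer choice, because it rests only on numbers already printed. The second depends on the 90% claim for 100 per arm.

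The cost is one sentence and a slightly less favourable dropout tolerance or power. It needs no extra participants and no change to the conduct of the trial.
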